### Secondary:{7b}

To document

- Reduction in the risk of disease progression
- Accelerated recovery
- Reduction in intensive supportive care and long-term hospitalization
- Clinical profile in terms of Siddha System of Medicine (SSM)
- Adverse events/effects if any

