### Sample size {14}

As there is no prior work on this research question, so no assumptions for the sample size calculation could be made. The present study will serve as a pilot trial. We intend to study 60 patients, each 30 in two groups.

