### Outcome assessment

Clinical outcomes: (i) Assessment of clinical symptoms (ii) Clinical profile of SSM (iii) Time to test COVID-19 Negative

Safety Assessment: (i) Elevation of ALT to more than five-fold upper normal limit; (ii) Anaphylaxis; and (iii) Adverse events and serious adverse events.

Laboratory outcomes: (i) Viral RNA loads and cycle threshold values in serial samples of nasopharyngeal

and oropharyngeal swabs and blood, collected every week (to document anti-viral activity). (ii) Immunoglobulins values in serial samples of serum collected every week (to document immunomodulatory effect)

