### Data collection {19}

At the time of recruitment, we will collect socio-demographics, history of illness and clinical examination. At every visit we will do systematic clinical examination, determine adherence to interventions and assessment about any complaints and any adverse events. Both allopathic and Siddha physicians will perform clinical examination and collect relevant details according to their systems.

**Baseline laboratory investigations:** (i) Haemogram; (ii) Liver function tests (LFTs); (iii) Renal function tests (RFTs); (iv) Haemoglobin A1c and blood sugar, (v) RT-PCR for SARS-CoV-2 (respiratory samples: nasopharyngeal swab, oropharyngeal swab, in addition, sputum, bronchoalveolar lavage (BAL), if available); (vi) electrolytes, (vii) Chest X-ray; (viii) Electrocardiogram (ECG) (ix) Immunoglobulins

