### Data Analysis plan {20}

The analysis plan on the primary and secondary outcome is described in the below table

Table 5: Statistical analysis plan{20a}

| Outcome                                                              | Hypothesis                                 | Outcome measure                                        | Methods of analysis            |
|----------------------------------------------------------------------|--------------------------------------------|--------------------------------------------------------|--------------------------------|
| Primary                                                       |                                            |                                                        |                                |
| Viral load of SARS-CoV-2                                             | Reduction of Viral Load after intervention | Viral Load                                             | T test                         |
| Immunological markers                                                | Improvement                                | Th1, Th2 cells                                         | T test                         |
| Secondary                                                     |                                            |                                                        |                                |
| Reduction in the risk of disease progression                         | Reduction of complication                  | Incidence of complication                              | Kaplan Meier survival analysis |
| Reduction in intensive supportive care and long-term hospitalization | Reduction of complication                  | Incidence of complication                              | Kaplan Meier survival analysis |
| Clinical profile in terms of Siddha System of Medicine (SSM)         |                                            | Questionnaire                                          | Chi-square test                |
| Adverse events/effects                                               |                                            | Presence of drug related adverse event (time to event) | Kaplan Meier survival analysis |

**Data monitoring {21a}:** The data safety monitoring committee constituted by Ministry of AYUSH will be responsible for the monitoring the data

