**Harms/ adverse reaction reporting {22}:** The adverse events will be documented for each patient and will be reported to Pharmacovigilance cell of Siddha Central Research Institute, Chennai

**Ethical approval {24}:** The study will be initiated after the approval of the Institutional Ethics Committee of Government Stanley Medical College, Chennai.

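### Table 5 gives the intensive-support and hospitalization row the measure of the disease-progression row, and narrows the safety measure to drug-related events

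*Protocol*

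**What the plan says.** The secondary objectives ({7b}) list disease progression and, as a separate item, intensive supportive care with long-term hospitalization. Safety is a further item, worded "Adverse events/effects if any".

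Table 5 then fixes a hypothesis, a measure and a method for most of these. For the row "Reduction in intensive supportive care and long-term hospitalization" the measure is "Incidence of complication" and the method is Kaplan-Meier. The disease-progression row directly above has the same entries. For adverse events the measure is "Presence of drug related adverse event (time to event", again by Kaplan-Meier.

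Elsewhere the protocol treats safety more broadly. Under Outcome assessment, the safety items are ALT above five times the upper normal limit, anaphylaxis, and "Adverse events and serious adverse events". Data collection {19} provides for "assessment about any complaints and any adverse events" at every visit. Harms/adverse reaction reporting {22} says "The adverse events will be documented for each patient". The Blinding section states that there is none. On size, the protocol says "We intend to study 60 patients, each 30 in two groups".

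**The concern.** Table 5 is where the protocol commits itself to an analysis for each outcome. If a row names the wrong measure, following the plan faithfully gives the wrong result.

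For the hospitalization row, two separate objectives would be reported from one and the same analysis. A reader of the results could take the second as evidence on hospital stay or intensive support, which it is not.

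For the safety row, the comparison would rest on a judgement of relatedness. Where the arm is known, attribution can differ between a herbal decoction and a vitamin-zinc supplement even if the true event rates are equal. A serious event or a marked ALT rise judged unrelated would not count in the one safety comparison that the table names.

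**Working it through.** The check is a comparison of text. The plan states no figure to reproduce on this point.

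**1. The two complication rows of Table 5, side by side**

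| Entry | Disease progression | Intensive support and hospitalization |
|---|---|---|
| Hypothesis | Fewer complications | Fewer complications |
| Measure | Incidence of complication | Incidence of complication |
| Method | Kaplan-Meier | Kaplan-Meier |

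All three entries agree, so the two rows specify one analysis. Table 5 has three Kaplan-Meier rows, and two of them coincide. The clinical outcomes under Outcome assessment (symptoms, Siddha clinical profile, time to a negative test) do not supply a measure of stay or support either. No readable section defines a complication in a way that would include them.

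**2. Scope of safety, section by section**

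| Section | Scope |
|---|---|
| Secondary objectives {7b} | Adverse events or effects, no relatedness condition |
| Outcome assessment | ALT threshold, anaphylaxis, adverse and serious adverse events, no relatedness condition |
| Data collection {19} | Any adverse event, each visit |
| Harms {22} | Adverse events documented per patient and reported |
| Table 5 | Drug-related events only |

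Table 5 alone adds the restriction. The narrowing therefore affects the analysis, not the collection or reporting.

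**3. Fit of the time-to-event form to the ALT item**

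Table 4 schedules liver function tests at day 0 and day 14 only, which leaves one scheduled value after baseline. For that item a count of patients per arm loses almost nothing compared with a survival curve.

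**4. What arithmetic can add**

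The documents give no event rates and no attribution rates, so the size of any bias cannot be calculated. Two facts follow from 30 patients per arm:

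- One patient is 1/30 = 3.3 percentage points. A patient whose only event is classed as unrelated lowers that arm's observed proportion by this amount.
- With no events in an arm, the upper limit of the exact two-sided 95% interval is 1 − 0.025^(1/30) = 0.116, or 11.6%. This shows the precision that the arm size allows. It is the same for related and for all events, so it does not measure the defect.

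**The case against.** The case for leaving the table alone has four parts.

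- **Safety data are not lost.** All adverse events are collected, documented and sent to a pharmacovigilance cell, and a data safety monitoring committee is named. Full descriptive tables are often left to a statistical analysis plan, which is not shown here. This stands against any inference that the ALT, anaphylaxis or unrelated serious events disappear from the trial. It does not remove the mismatch between Table 5 and the protocol's own safety outcomes.
- **The assessor of relatedness is not named.** A reader might infer that unblinded staff make the call. The protocol does not say so, and physicians of both systems examine the patients. What can be said is that the trial has no blinding and that no blinded causality assessment is described. That is enough for a risk of bias, but not for its direction or size.
- **Text has been lost.** Part of the interventions section is illegible, so one cannot claim that the protocol nowhere defines a complication or a measure of stay. A reader might also infer that hospital stay will never be reported. The secondary aims are introduced as things to document, in a self-declared pilot, and simple reporting could partly serve them. The duplication inside Table 5 is nonetheless plain.
- **The remedy has the same weakness.** Discharge is also decided with the arm known, so time to discharge is not free of open-label influence. This is correct and should be acknowledged. It is still a measure of the stated outcome, which the present entry is not.

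**Conclusion.** The point holds in this form. The hospitalization row of Table 5 repeats the progression row and does not measure its own outcome. The safety row is narrower than the protocol's safety objective and safety assessment, and it makes the comparison depend on a causality judgement in an open-label trial. Both are stated rules that give a worse result if followed, not details left for later.

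The importance is moderate: secondary outcomes only, in a pilot of 60 patients. The conclusion rests on the current text of Table 5 and of the sections set beside it, and on no assumed event rate. It does not extend to a claim that safety data will be discarded, that named staff will misattribute events, or that the bias favours one arm. A statistical analysis plan could add the missing analyses, but the contradiction within the protocol would remain until Table 5 is amended.

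**What to change.** **(a) Hospitalization row.** Replace the measure with two of its own: time from randomisation to discharge, and receipt of intensive support (yes/no), each compared between arms. Time to discharge should run over the whole follow-up. The interventions section sets 14 days of therapy and 14 days after it, so a cut at day 14 would truncate the long stays that the outcome is about. State how transfer to another facility is counted, so that it is not read as early discharge, and note that discharge is an open-label decision.

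**(b) Safety row.** Replace the measure with all adverse events and serious adverse events regardless of causality, plus the ALT and anaphylaxis items from Outcome assessment. Report the number and percentage of patients per arm with exact 95% confidence intervals. A time-to-event display may be kept. Show drug-related events as a supplementary subset.

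**Cost.** Part (b) is wording only, since all adverse events are already collected and liver function is already tested at day 14. Part (a) is wording plus, if they are not already recorded, the discharge date and one yes/no field. Patients are monitored daily until discharge, so the date should be easy to obtain, but no readable section lists intensive support as a recorded item.

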### Consent for the trial and biological specimen testing {26}

The purpose of the trial will be explained to all eligible SARS-CoV-2 confirmed patient. Informed consent will be obtained from all eligible participants willing to participate in the trial. Each participant will be informed that participation in the trial is voluntary and that s/he is free to withdraw, without justification, from the trial at any time without consequences and without affecting professional responsibilities. Informed consent will seek approval to collect blood samples and clinical data for the intended purpose of this trial.

### Risks and benefits for subjects

This investigation poses minimal risk to participants, involving the collection of a small amount of blood. The direct benefit to the participant is the ability to detect SARS-CoV-2 viral load which would allow for appropriate monitoring and treatment. The primary benefit of the study is indirect in that data collected will help to find an intervention for the management of COVID-19.

### **Confidentiality{27}**

Participant confidentiality will be maintained throughout the investigation. All subjects who participate in the investigation will be assigned a study identification number by the investigation team for the labelling of questionnaires and clinical specimens. The link of this identification number to individuals will be maintained by the investigation team and the CCRS and will not be disclosed elsewhere.

Study will be conducted according to AYUSH GCP guidelines.

**Declaration of Interests {28}:** All investigators don't have any conflict of interest with the study involved.

